### 9.3.2 Adverse Event (AE) and Serious Adverse Event (SAE) Documentation and Reporting

All observed AE regardless of treatment group or suspected causal relationship to study drug will be assessed following NCI-CTCAE version 4.0 and recorded on the AE page of the CRF, and in the case of a serious adverse event will also be recorded on a SAE form.

All SAEs must be reported immediately (i.e., within 24 hours of the Investigator's knowledge of the event) by facsimile of the SAE Report Form to the Würzburg Study Centre (Endocrinological Trial Unit):

**Universitätsklinikum Würzburg**  
**Medizinische Klinik und Poliklinik I**  
**Endokrinologische Studienambulanz**  
**[name]**  
**[name], Germany**  
**[contact]**  
**[contact]**  
**E-mail: [contact]**

A diagnosis or syndrome should be recorded on the AE page of the CRF rather than the individual signs or symptoms of the diagnosis or syndrome.

An overdose, accidental or intentional, whether or not it is associated with an AE, or abuse, withdrawal, sensitivity or toxicity to an investigational medicinal product should be reported as an AE. If an overdose is associated with an AE, the overdose and adverse event should be reported as separate terms.

In the event of overdose or exaggerated response, the subject should be monitored as appropriate and should receive supportive measures as necessary. There is no known specific antidote for overdose. Actual treatment should depend on the severity of the clinical situation and the judgment and experience of the treating physician.

Worsening/exacerbation of signs and symptoms (in terms of severity and/or frequency, or the appearance of new manifestations/complications) of the neoplasia under study or of a pre-existing illness should be reported as an AE in the appropriate section of the CRF – but are not considered as SAEs (refer to 9.1.2 Serious Adverse Events).

In addition, clinically significant changes in physical examination findings and abnormal objective test findings (e.g., X-ray, ECG) should also be recorded as AEs. The criteria for determining whether an abnormal objective test finding should be reported as an AE are as follows:

Test result leads to a change in study dosing or discontinuation from the study, significant additional concomitant drug treatment or other therapy, and/or test result leads to any of the outcomes included in the definition of a SAE, and/or test result is considered to be an AE by the investigator or sponsor.

If an abnormal laboratory value is associated with a diagnosis or clinical sign/symptom, the diagnosis or sign/symptom should be reported as an AE and the associated laboratory result should be considered additional information to support the diagnosis.

For all AEs, the investigator must pursue and obtain adequate information both to determine the outcome of the AE and to assess whether it meets the criteria for classification as a SAE requiring immediate notification to the Würzburg Study Center (Endocrinological Trial Unit). Sufficient information should be obtained by the investigator to determine the causality of the AE (i.e., study drug or other illness). The investigator is required to assess causality and indicate that assessment on the CRF. All AEs and especially those that are serious, suspected to be related to study drug or considered significant by the investigator or clinical monitor must be followed after the time of therapy discontinuation until the event or its sequelae resolve or stabilize at a level acceptable to the investigator and the clinical monitor or his/her designated representative. All AEs will be recorded in the CRF.

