## **9 ADVERSE EVENTS AND SERIOUS ADVERSE EVENTS**

### **9.1 Definition**

#### **9.1.1 Adverse Event (AE)**

An Adverse Event (AE) is any new untoward medical occurrence or worsening of a pre-existing medical condition in a patient or clinical investigation subject administered an investigational (medicinal) product. An AE can therefore be any unfavourable and unintended sign (including abnormal laboratory findings for example), symptom, or disease temporally associated with the use of a medical product, whether or not a causal relationship (i.e. related/not related) with the treatment is suspected.

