#### **9.1.2 Serious Adverse Event (SAE)**

A Serious Adverse Event (SAE) is any untoward medical occurrence that at any dose:

- is fatal (results in death)
- is life-threatening
- requires or prolongs in-patient hospitalization
- results in persistent or significant disability / incapacity
- is a congenital anomaly / birth defect
- is medically significant (defined as any clinical event or laboratory result that may not be immediately life-threatening or result in death or hospitalization but, based upon appropriate medical and scientific judgment, may jeopardize the subject or may require intervention (e.g. medical, surgical) to prevent one of the other serious outcomes listed in the definition above. Examples of such events include but are not limited to, allergic bronchospasm requiring intensive treatment in an emergency room or at home, blood dyscrasia or convulsions that do not result in inpatient hospitalization, development of drug dependency or drug abuse)

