**A SAE judged as potentially related to a study drug qualifies as Serious Adverse Drug Reaction (SADR).**

**Events exclusively related to tumor relapse/progression or treatment of tumor relapse/progression are not considered SAEs.**

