**NOTE:**

The following hospitalizations are **not** considered SAEs:

- A visit to the emergency room or other hospital department for less than 24 hours that does not result in admission (unless considered a “medically significant event” or a “life-threatening event”)
- Outpatient or same-day or ambulatory procedures
- Observation on short-stay units
- Hospitalization due to diagnostic procedures or standard supportive care (e.g. implant of central venous catheter, routine treatment or monitoring of the studied indication not associated with any deterioration in condition).
- The administration of blood or platelet transfusion as routine treatment of studied indication. However, hospitalization or prolonged hospitalization for a complication of such transfusion remains a reportable SAE.
- A pre-planned hospitalization for a condition which existed at the start of study drug and which did not worsen during the course of study drug treatment (e. g. scans, endoscopy, sampling for laboratory tests...). However, hospitalization or prolonged hospitalization for a complication of such procedures remains a reportable SAE.
- Social admission (e.g. subject has no place to sleep; hospice facilities)
- Administrative admission (e.g. for yearly physical examinations)
- Protocol-specified admission during a clinical trial (e.g. for a procedure required by the study protocol or for clinical research)
- Optional admission not associated with a precipitating clinical AE (e.g. for elective cosmetic surgery)

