#### 9.3.4 Causality assessment

The Investigator must determine the relationship between the administration of IMP and the occurrence of an AE/SAE as not related or related as defined below:

|                     |                                                                                                                                                                                                                                                                 |
|---------------------|-----------------------------------------------------------------------------------------------------------------------------------------------------------------------------------------------------------------------------------------------------------------|
| Not related: | The temporal relationship of the adverse event to IMP administration makes a causal relationship unlikely or remote , or other medications, therapeutic interventions, or underlying conditions provide a sufficient explanation for the observed event. |
| Related:     | The temporal relationship of the adverse event to IMP administration makes a causal relationship possible , and other medications, therapeutic interventions, or underlying conditions do not provide a sufficient explanation for the observed event.   |

If an event is assessed as suspected of being related to a comparator, ancillary or additional IMP that has not been manufactured or provided by the sponsor, please provide the name of the manufacturer when reporting the event.

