## **9.5 Responsibilities of the Coordinating Investigator**

### **Suspected Unexpected Serious Adverse Reactions (SUSARs)**

#### **9.5.1 Definition of SUSARs**

Suspected Unexpected Serious Adverse Drug Reactions are side effects (probably or definitely connected with the administration of the investigational product), the nature or severity of which are inconsistent with the information available about the product. Information about the investigational product is contained in the Investigational Medicinal Product Dossier/Summary of Product Characteristics.

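### Section 9.3.2 takes serious worsening of a pre-existing illness out of SAE status, against Section 9.1.2; the SUSAR wording in 9.5.1 also does not match the causality scale in 9.3.4

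*Protocol*

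**What the plan says.** On seriousness, Section 9.1.1 counts as an AE "any new untoward medical occurrence or worsening of a pre-existing medical condition in a patient". Section 9.1.2 opens its definition with "A Serious Adverse Event (SAE) is any untoward medical occurrence that at any dose" and lists the usual criteria, including death and hospitalization. Its one disease-related exception is "Events exclusively related to tumor relapse/progression or treatment of tumor relapse/progression are not considered SAEs". Its note on hospitalizations exempts a pre-planned stay for an existing condition, but only for a condition "which did not worsen during the course of study drug treatment", and it keeps complications of such stays reportable.

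Section 9.3.2 then covers worsening, including greater severity or frequency and new complications, "of the neoplasia under study or of a pre-existing illness should be reported as an AE in the appropriate section of the CRF", and closes the sentence with "but are not considered as SAEs (refer to 9.1.2 Serious Adverse Events").

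On causality, Section 9.1.2 uses potential relatedness as the threshold for a serious adverse drug reaction. Section 9.3.4 gives the investigator two categories. The related category requires that timing makes "a causal relationship possible" and that no other factor sufficiently explains the event. Section 9.5.1 describes SUSARs as "side effects (probably or definitely connected with the administration of the investigational product"). Section 9.5.2 sends SUSARs to the authority, the ethics committee and the investigators within 15 days.

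**The concern.** Section 9.3.2 cites 9.1.2 as the basis for an exemption that 9.1.2 does not give. Two investigators can follow the protocol, each relying on a different section, and classify the same event differently. With about 15 centres, inconsistent handling is a realistic prospect.

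What is at stake is the speed and correct labelling of safety information on an investigational tracer. Section 3.3.3 makes serious adverse reactions to the tracer a ground for considering termination, and that safeguard works only if serious events are classified as such. As worded, the 9.3.2 exemption carries no condition on outcome, seriousness or suspected relation to the tracer.

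The SUSAR wording raises a smaller question one step later: once an event is an SAE and rated related, does it go forward within 15 days if it is unexpected?

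**Working it through.** No arithmetic applies. The check sets the passages side by side and follows two example events through the reporting rules.

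**Event A: a comorbidity present at consent worsens before Visit 4, and the patient is hospitalized or dies.**

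1. Section 9.1.1: worsening of an existing condition is an AE.
2. Section 9.1.2, main definition: the hospitalization or death criterion is met, so it is an SAE.
3. Section 9.1.2, disease-related exception: not applicable, because the event is not due solely to the tumour's relapse or progression or its treatment.
4. Section 9.1.2, hospitalization note: the exemption for pre-planned stays does not apply, because the condition did worsen.
5. Section 9.4: as an SAE it must be reported within 24 hours, whatever the cause.
6. Section 9.3.2: the same event is an AE on the CRF and not an SAE. The SAE form and the 24-hour report apply only to SAEs, so neither is triggered, and no SUSAR assessment follows.

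Steps 2 to 5 and step 6 give opposite answers for the same event.

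**The neoplasia limb of the same sentence.** Section 9.3.2 also exempts any worsening or new complication of the neoplasia. Section 9.1.2 exempts only events due exclusively to relapse or progression, or its treatment. A serious tumour complication that is not exclusively progression is an SAE under 9.1.2 and not under 9.3.2. The two sections therefore differ on the tumour as well, to a smaller extent.

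**Event B: an unexpected SAE with plausible timing and no sufficient alternative explanation.**

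1. Section 9.3.4: it is rated related.
2. Section 9.1.2: it is potentially related, hence a serious adverse drug reaction.
3. Section 9.4: it reaches the study centre within 24 hours.
4. Section 9.5.1: it is a SUSAR only if probably or definitely connected. The investigator's scale has no such grades, so the recorded rating does not settle the question.
5. Section 9.5.2: the 15-day route is for SUSARs, and the quarterly table is for SAEs considered unrelated. If event B is held not to be a SUSAR, it is in neither.

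**Where the events still appear.** Event A stays on the CRF (9.3.2), is graded for severity up to grade 5 for death (9.3.3), and belongs in the AE tables (8.6) and in the AE listing sent to the IDMC every 12 months (11.2). Event B remains an SAE throughout.

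**The case against.** The best defence is that 9.1.2 was meant to govern. Section 9.3.2 refers the reader to it. The same section requires every AE to be assessed against the SAE criteria, and 9.4 asks for all SAEs whatever the circumstances. One can also argue that 9.3.2 speaks of signs and symptoms while 9.1.2 turns on outcomes. This makes systematic loss of SAEs less certain. It does not remove the conflict: 9.3.2 tells the investigator the answer for this class of events, the cited section says otherwise, and the protocol states no order of precedence.

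On causality, the defence is stronger. The related category in 9.3.4 needs both plausible timing and the absence of a sufficient alternative explanation, which is stricter than bare possibility and may come close to probable. Events that are possible but otherwise explained are rated unrelated anyway. Every event classed as an SAE still reaches the study centre within 24 hours. What stands is a mismatch of terms that leaves onward expedited reporting unclear.

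A reader might infer that serious reactions would go unreported, that the IDMC's AE listing would be incomplete, or that the safety tables would lose events. The document does not support this. Events exempted by 9.3.2 are still recorded, listed and tabulated as AEs; what could fall short is the SAE reports and the SAE count. The SUSAR wording cannot change SAE counts at all.

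**Conclusion.** The contradiction between 9.3.2 and 9.1.2 is real and is in the current text. Its effect is misclassification and missing 24-hour reporting of serious worsening of a comorbidity, and to a lesser degree of serious tumour complications that are not exclusively progression. It is not a loss of the events from the data.

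The mismatch between 9.5.1 and 9.3.4 (and with potential relatedness in 9.1.2) is separate and carries less weight. It would be too strong to say that every event rated related falls outside the SUSAR definition; the document leaves this undetermined.

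The protocol gives no comorbidity or event rates, so the size cannot be estimated. The conclusion assumes that some investigators would apply 9.3.2 as written. The point concerns safety reporting only and does not affect the sample size or the confirmatory tests.

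**What to change.** Reconcile the passages in one amendment.

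- **Section 9.3.2:** keep the instruction to record worsening of the neoplasia or of a pre-existing illness as an AE. Replace the closing exemption with a statement that SAE status is decided by 9.1.2, whose only disease-related exception is for events due exclusively to tumour relapse or progression or its treatment. Merely striking the reference to pre-existing illness would not be enough: it would drop the explicit recording instruction for those events and leave a neoplasia exemption wider than that of 9.1.2.
- **Section 9.5.1:** align the causality wording with the related category of 9.3.4, so that the investigator's recorded rating feeds directly into the SUSAR decision.
- **Data already collected:** re-screen AEs on the paper CRFs against the reconciled rule and complete SAE reports where one was due.

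The cost is a short amendment, one query round and slightly more SAE forms.

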### 9.3.3 Severity assessment

For both AEs and SAEs, the Investigator must assess the severity of the event.

The severity of AEs will be graded based upon the subject's symptoms according to National Cancer Institute (NCI) Common Terminology Criteria for Adverse Events (CTCAE, Version 4.0); <http://ctep.cancer.gov/reporting/ctc.html>.

AEs that are not defined in the NCI CTCAE should be evaluated for severity according to the following scale:

- **Grade 1 = Mild** – transient or mild discomfort; no limitation in activity; no medical intervention/therapy required
- **Grade 2 = Moderate** – mild to moderate limitation in activity, some assistance may be needed; no or minimal medical intervention/therapy required
- **Grade 3 = Severe** – marked limitation in activity, some assistance usually required; medical intervention/therapy required, hospitalization is possible
- **Grade 4 = Life threatening** – extreme limitation in activity, significant assistance required; significant medical intervention/therapy required, hospitalization or hospice care probable
- **Grade 5 = Death** – the event results in death

#### 9.3.4 Causality assessment

The Investigator must determine the relationship between the administration of IMP and the occurrence of an AE/SAE as not related or related as defined below:

|                     |                                                                                                                                                                                                                                                                 |
|---------------------|-----------------------------------------------------------------------------------------------------------------------------------------------------------------------------------------------------------------------------------------------------------------|
| Not related: | The temporal relationship of the adverse event to IMP administration makes a causal relationship unlikely or remote , or other medications, therapeutic interventions, or underlying conditions provide a sufficient explanation for the observed event. |
| Related:     | The temporal relationship of the adverse event to IMP administration makes a causal relationship possible , and other medications, therapeutic interventions, or underlying conditions do not provide a sufficient explanation for the observed event.   |

If an event is assessed as suspected of being related to a comparator, ancillary or additional IMP that has not been manufactured or provided by the sponsor, please provide the name of the manufacturer when reporting the event.

#### 9.3.5 Duration

The Investigator will provide a record of the start and stop dates of the AE/SAE. The duration of the AE and the SAE may vary within one event. For example, a non-serious AE may begin on 01-Jan. The event will become serious when it meets one of the criteria for seriousness (e.g., the subject is hospitalized on 05-Jan). The SAE will continue until it no longer meets the seriousness criteria (e.g., the subject is discharged on 07-Jan). However, the AE continues until 10-Jan when the event resolves. The AE dates may extend from before and beyond the SAE dates, but not the reverse.

#### 9.3.6 Action Taken

The Investigator will report the discontinuation or reduction of IMP following an AE and report if concomitant and/or additional treatments were given for the AE.

#### 9.3.7 Outcome

All SAEs that have not resolved upon discontinuation of the subject's participation in the study must be followed until recovered, recovered with sequelae, not recovered (death due to another cause) or death (due to the SAE).

## 9.4 Expedited Reporting of Adverse Events

All Serious Adverse Events (SAE), related or not to study drugs, occurring at any time during the study – from date of informed consent to V4 (follow up) - independent of the circumstances or suspected cause, must be reported, within 24 hours of knowledge by fax.

The investigator must fill in the SAE Form in English and assess the relationship to the IMP, and send it signed and dated, within 24 hours of learning of its occurrence, even if it does not appear to be treatment-related, to the Würzburg Study Center (Endocrinological Trial Unit) at the University Hospital of Würzburg.

Any late Serious Adverse Drug Reaction (SADR), occurring after the Follow-up period also must be reported to the Würzburg Study Center (Endocrinological Trial Unit) at the University Hospital of Würzburg.

Information collected in the SAE form is crucial to assess the case. For this reason, diligences in collecting as much verifiable and reliable information are needed: both, quality and timeliness are key factors. If known, the diagnosis of the underlying illness or disorder should be recorded, rather than its individual symptoms. The following information should be captured for all SAEs: onset, duration, severity, seriousness, relationship to study drugs, action taken and treatment required.

The investigator must also attach the following whenever possible:

- a copy of the summary of hospitalization or prolongation of hospitalization
- a copy of the post-mortem report (if applicable)
- a copy of all relevant laboratory examinations and the dates on which these examinations were carried out, including relevant negative results as well as normal laboratory ranges
- all other documents that are judged useful and relevant

All these documents will remain pseudonymized.

### Follow-up information

The investigator is responsible for the appropriate medical follow-up of patients until resolution or stabilization of the adverse event or until the patient's death. This may mean that follow-up should continue once the patient has left the trial. Follow up information about a previously reported SAE must be reported by the investigator to the Endocrinological Trial Unit **within 24 hours** of receiving it (at latest on the next working day), on the serious adverse event report form, by ticking the box marked "Follow-up N°...". The investigator also transmits the final report at the time of resolution or stabilization of the SAE. The investigator retains the documents concerning the supposed serious adverse event so that previously transmitted information can be completed if necessary.

